**Figure 1 figure1:**
[figure not shown]
PLATINUMS (Implementation of an Advanced Telerehabilitation Solution for People With Multiple Sclerosis) project overview based on working packages (WPs). DMSH: Danish Multiple Sclerosis Hospitals; FAIR: findable, accessible, interoperable, and reusable; RCT: randomized controlled trial; TAU: Tel Aviv University; UC: University of Cagliari; UL: University of Limerick.

**Table 1 table1:** PLATINUMS (Implementation of an Advanced Telerehabilitation Solution for People With Multiple Sclerosis) Gantt chart describing each working package (WP) and task (T).

		Year 1					Year 2					Year 3			
		Q1	Q2	Q3	Q4	Q5		Q6	Q7	Q8	Q9		Q10	Q11	Q12
**WP1: Ethical approval, staff recruitment**		✓													
**WP2: International usability and feasibility study of the telerehabilitation system**			✓	✓	✓	✓									
	T2.1. Installation of the telerehabilitation system, including private data security and cloud data management		✓												
	T2.2. Harmonization between staff members operating the telerehabilitation system and intervention program		✓												
	T2.3. Testing the system on a small group of participants for feasibility (patient/therapist), integrity, security, and proper transfer of data			✓	✓	✓									
**WP3: Development and validation study of balance and mobility functional tests delivered remotely**			✓	✓	✓	✓		✓							
	T3.1. Development of mobility assessment tests to be delivered remotely via the telerehabilitation system		✓	✓											
	T3.2. Establishing reliability and validity of the remote mobility tests			✓	✓	✓		✓							
	T3.3. Developing standardized instructions and training materials							✓							
**WP4: Efficacy study of the telerehabilitation study via a pilot multicenter RCT^a^**								✓	✓	✓	✓		✓	✓	
	T4.1. Coordination between staff members operating the intervention programs and blind assessors on all procedures related with the outcome measures							✓							
	T4.2. Implementation of intervention programs							✓	✓	✓	✓		✓		
	T4.4. Data analysis of remote and clinical outcome measures												✓	✓	
	T4.5. Assessing adherence to and satisfaction with (among participants/therapists) the telerehabilitation intervention program												✓	✓	
**WP5: Economic evaluation of the telerehabilitation system**								✓	✓	✓	✓		✓	✓	
	T5.1. Identifying the perspective of the economic evaluation and finalizing the specific study questions in terms of economics							✓							
	T5.2. Identifying all the costs associated with the implementation of the telerehabilitation system and intervention program							✓							
	T5.3. Following costs of the RCT and identifying all the benefits of the telerehabilitation system and intervention program							✓	✓	✓	✓		✓		
	T5.4. Cost-effectiveness (cost-utility) analyses													✓	
	TS.5. Interpretation and reporting of results														✓
**WP6: Data management adhering to the FAIR^b^ data management principles**		✓	✓	✓	✓	✓		✓	✓	✓	✓		✓	✓	✓
**WP7: Coordination, management, and dissemination**		✓	✓	✓	✓	✓		✓	✓	✓	✓		✓	✓	✓
	17.1. Dissemination of project findings								✓	✓	✓		✓	✓	✓
Meetings		F^c^	O^d^	O	O	O		F	O	O	O		O	O	F

^a^RCT: randomized controlled trial.

^b^FAIR: findable, accessible, interoperable, and reusable.

^c^F: face-to-face.

^d^O: online.

### Research and Innovation Questions

This innovative project will include 5 key research questions (RQs), which we propose will fill in the gaps in our current knowledge.

RQ1 (WP2) is as follows: In people with MS, what is the usability and feasibility of an advanced telerehabilitation system in facilitating remote exercise training? Qualitative and quantitative measures will be used to evaluate the usability and feasibility of the telerehabilitation system in 4 countries. Following necessary system upgrades and adaptations, findings will be incorporated into the feasibility multicenter RCT (WP4). Based on data from other patient populations, we hypothesize that the innovative telerehabilitation system will score highly for usability and feasibility among the participants with MS.

RQ2 (WP3) is as follows: In people with MS, are scores provided by clinical mobility tests obtained via tele-rehabilitation valid and reliable? Evidence for remote mobility evaluation does not currently exist for people with MS. We will evaluate 5 tests developed from commonly used clinical measures. We hypothesize that innovative remote mobility tests will demonstrate good-to-excellent validity and reliability.

RQ3 (WP4) is as follows: In people with MS, is a large multicenter RCT possible, and can it show preliminary efficacy of an individualized exercise program delivered via telerehabilitation to improve mobility compared with in-person physical therapy? An international pragmatic multicenter feasibility RCT will be conducted to compare the effectiveness of delivering the individual exercise program via telerehabilitation versus in person by a physiotherapist. We hypothesize that both exercise intervention programs will improve mobility in people with MS; however, nonsignificant differences in mobility outcome measures between groups (telerehabilitation vs usual care) will be demonstrated.

RQ4 (WP4) is as follows: In people with MS, does an individualized exercise program delivered via telerehabilitation have a comparable effect on mood and quality of life (QoL) compared with standard physical therapy (facility based)? This RQ will be answered in the planned international multicenter feasibility RCT, preceded by a feasibility and usability study. Consequently, our hypothesis is that mood and QoL will be improved in participants whose symptoms are significant at baseline.

RQ5 (WP5) is as follows: In people with MS, does a personalized exercise program delivered via telerehabilitation yield comparable cost-effectiveness value compared with standard physical therapy (facility based)? We hypothesize that the telerehabilitation system will be more cost-effective than personal exercise provided by a physiotherapist. We will account for several potential confounders, such as (1) disability, (2) geographic location, and (3) comorbidities.

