## Methods

### Overview

Our main objective is to collect evidence to facilitate the implementation of an innovative AI telerehabilitation exercise training system in MS clinical practice. After the completion of working package (WP) 1, which focuses on obtaining ethical approval and recruiting staff, our first objective (WP2) will be to investigate the usability and feasibility of the WizeCare system in MS centers in 4 European countries, encompassing a range of people with MS with varying disabilities and demographics. The second objective (WP3) will be to develop and psychometrically test a range of mobility measures collected by the telehealth system. The third objective (WP4) will be to compare exercise delivered via telehealth with usual care. The primary outcome will be trial feasibility, with preliminary efficacy for mobility, mental health, social participation, and quality of life outcomes. The fourth objective (WP5) will be to conduct an economic evaluation of exercise program delivery via telehealth compared with in-person care. The final objective will be to work collaboratively with clinicians, policymakers, and people with MS and to widely disseminate the knowledge generated by this program to optimize implementation. Figure 1 presents the WPs of the PLATINUMS (Implementation of an Advanced Telerehabilitation Solution for People With Multiple Sclerosis) project, while Table 1 illustrates its expected timeframe.

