In parallel with the system feasibility and usability study, we plan to develop and psychometrically test a set of remote balance and functional mobility tests delivered via the telerehabilitation system (WP3). We will adapt and manualize 5 remote mobility tests that are collected through the telerehabilitation system: the 30-second sit-to-stand (30STS) test, timed-up-and-go (TUG) test, functional reach test (FRT), 20-second single-leg stance (20SLS) test, and the Short Physical Performance Battery (SPPB). The SPPB includes the following tests: side-by-side stand (10 seconds), semitandem stand (10 seconds), tandem stand (10 seconds), a gait speed test over 3 meters, and a 5-time repeated chair stand test. Upon completion of the developmental phase, we will conduct a test-retest reliability study for in-person and telehealth data capture and a criterion validity study comparing telehealth and in-person data with 15 people with MS (EDSS 2.5-6.5) at each site (n=60).

To examine the efficacy of the advanced telerehabilitation solution for people with MS, we propose an international feasibility multicenter RCT (WP4). We will include a target sample of 24 participants per country (in 4 countries; 96 participants in total) based on the stepped rule of thumb proposed by Whitehead et al [33], who estimated the optimal sample size for an early-stage/pilot RCT to be 24. Importantly, as the results may differ across countries, we consider each country an individual site for the feasibility RCT. Statistical analysis will be performed for the total group and each country separately. The participants will be randomly allocated (individual randomization) into one of two groups: (1) home-based telerehabilitation exercise training via the WizeCare platform [28] or (2) usual care. The sample criteria for the feasibility multicenter RCT will be the same as those for WP2.

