**Figure 2 figure2:**
[figure not shown]
Key elements of the telerehabilitation digital platform.

The telerehabilitation exercise intervention program will comprise a 10-week, physiotherapist-prescribed, evidence-based, individualized exercise program based on the exercise guidelines for people with MS and the physiotherapist’s clinical reasoning [34]. Eligible participants will receive tailored exercise instructions, which will include performing 8 to 10 exercises in accordance with their abilities and functional needs. Following the first week of training, the participant will be contacted by a physical therapist (via video or audio chat through the system) to monitor participation, progress, and adverse events. Participants in the telerehabilitation group will be compared to those in usual care. Since the term “usual care” is broad, particularly across countries, and physical activity participation varies, participants in both groups will provide weekly information about their physical activity based on the FITT-VP (frequency, intensity, time, type, volume, and progression) principles [35]. To measure adherence, all participants will receive a diary and be requested to log their exercises and submit reports weekly. The report submission will be monitored weekly with a phone call by a physical therapist.

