### Data Analysis and Statistical Plan

Each research question is addressed through specific outcome measures. For RQ1, usability and feasibility will be assessed via the TUQ, adherence rates, dropout rates, and stakeholder interviews, with qualitative data analyzed thematically. RQ2 involves psychometric evaluation of remote assessments (e.g., SPPB, STS, and TUG) using intraclass correlation coefficients for test-retest reliability and Pearson correlations to compare remote and in-person scores. RQ3 and RQ4 outcomes (eg, 30STS, MSWS-12, EQ-5D-5L, STAI, and QIDS) will be analyzed using linear mixed models to assess within- and between-group effects over time. The primary analysis will follow an intention-to-treat principle, including all randomized participants in the groups to which they were originally assigned, regardless of adherence to the intervention protocol. A per-protocol analysis may be conducted as a secondary exploratory analysis. Missing data will be addressed using multiple imputation, assuming data are missing at random, and sensitivity analyses will be performed to assess the robustness of results.

As part of RQ5, the study also incorporates a comprehensive economic evaluation of the telerehabilitation system, which complements the clinical analyses and addresses a critical gap in MS rehabilitation research. A cost-utility analysis will be conducted to compare the telerehabilitation intervention and usual care, using incremental cost-effectiveness ratios derived from health care service use data and EQ-5D-5L–based quality-adjusted life years. Cost data will include implementation, infrastructure, maintenance, training, support services, and any differences in health service use or patient-reported outcomes. These data will be collected alongside the RCT to ensure alignment between clinical effectiveness and economic impact.

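### The WP4 comparator is usual care in the allocation and analysis text but in-person physiotherapy in RQ3 to RQ5 and the WP5 objective; the two must be reconciled

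*Protocol article*

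**What the plan says.** The protocol article describes the control side of WP4 in two ways.

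**Usual care**
- Methodology, Approach, and Study Population: participants are individually randomised to "home-based telerehabilitation exercise training via the WizeCare platform [28] or (2) usual care".
- Intervention and Comparators: "Participants in the telerehabilitation group will be compared to those in usual care". The same paragraph continues: "Since the term “usual care” is broad, particularly across countries, and physical activity participation varies, participants in both groups will provide weekly information".
- Data Analysis and Statistical Plan: the cost-utility analysis will "compare the telerehabilitation intervention and usual care".
- The Abstract, the aim in the Introduction and the WP4 objective in the Overview also name usual care.

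**In-person or facility-based physiotherapy**
- Research and Innovation Questions, RQ3: the trial will "compare the effectiveness of delivering the individual exercise program via telerehabilitation versus in person by a physiotherapist". The RQ3 hypothesis treats both arms as exercise programmes that will improve mobility.
- RQ4 and RQ5: the comparator is standard facility-based physical therapy. The RQ5 hypothesis names exercise provided by a physiotherapist.
- Overview, WP5 objective: "economic evaluation of exercise program delivery via telehealth compared with in-person care".

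RQ3 uses both descriptions in one paragraph. After the in-person wording, its hypothesis labels the same two groups telerehabilitation versus usual care.

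**The concern.** These are two different contrasts. One compares two ways of delivering an individualised exercise programme. The other compares a telerehabilitation programme with whatever patients would otherwise receive, which for some may be no physiotherapy.

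The stake is interpretation. RQ3 predicts a nonsignificant between-group difference in mobility. Against an active in-person arm, such a result would at least bear on whether the delivery modes are comparable. Against undefined usual care, it could equally mean that the programme adds nothing to what patients already receive. Conversely, an advantage over usual care would say little about how telerehabilitation compares with a physiotherapist in the room. For RQ5, the incremental cost depends heavily on how many physiotherapist sessions controls actually receive. The Discussion says the results should inform a fully powered trial, which would inherit the ambiguity.

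**Working it through.** **Step 1: the plan's own figure.** The WP4 sample is 24 participants per country in 4 countries: 24 × 4 = 96, as stated. The 24 comes from a cited rule of thumb. No effect size, SD or margin is attached to it, so the sample size does not show which contrast was intended.

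**Step 2: can the two descriptions be the same thing?** They would be if usual care were defined as in-person physiotherapy. Three places in the article bear on this.
- Intervention and Comparators gives usual care no content. It acknowledges variation between countries and responds by recording physical activity weekly in both groups.
- The WP4 eligibility criteria are those of WP2: age, diagnosis, EDSS 2.5 to 6.5, willingness to travel for evaluations, internet and device, no recent relapse, and ability to follow instructions. None requires current physiotherapy.
- The Abstract and Introduction justify the project by the poor accessibility of facility-based exercise. On that premise, some controls may receive none.

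Nothing in the article equates the two comparators.

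**Step 3: what the randomised contrast estimates.** Let B be the benefit of in-person therapy in SD units, g the true difference of telerehabilitation minus in-person therapy, and p the share of controls receiving in-person therapy. Controls without it are taken to gain nothing. Then

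contrast = (B + g) − pB = g + (1 − p)B.

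For B > 0 this equals g, the quantity in RQ3, only when p = 1. The documents give no value for B, g or p, so all values below are assumptions.

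| p | B = 0.5, g = 0 | B = 0.5, g = −0.2 | B = 0.3, g = 0 | B = 0.3, g = −0.2 |
|---|---|---|---|---|
| 0 | 0.50 | +0.30 | 0.30 | +0.10 |
| 0.25 | 0.375 | +0.175 | 0.225 | +0.025 |
| 0.5 | 0.25 | +0.05 | 0.15 | −0.05 |
| 0.75 | 0.125 | −0.075 | 0.075 | −0.125 |
| 1 | 0.00 | −0.20 | 0.00 | −0.20 |

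The contrast is zero at p = 1 + g/B. With g = −0.2 this is 1 − 0.2/0.5 = 0.60 for B = 0.5, and 1 − 0.2/0.3 = 0.33 for B = 0.3. Below that share, telerehabilitation looks better than control while being worse than in-person therapy. At that share the expected difference is nil although the modes differ by 0.2 SD.

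**Step 4: pooling over countries.** Take B = 0.5, g = 0 and p = 0, 0.25, 0.75 and 1 in four equal countries. The pooled contrast is (0.50 + 0.375 + 0.125 + 0)/4 = 0.25. Only the country with p = 1 estimates the comparison of delivery modes.

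**The case against.** The strongest defence is that the authors mean one thing throughout. RQ3 labels the groups as usual care directly after the in-person wording, and RQ4 and RQ5 speak of standard therapy. Usual care may therefore be shorthand for usual physiotherapy, with the variation between countries being variation in that physiotherapy. A fuller protocol might define it. This reading is possible, and under it the contrast would serve RQ3 to RQ5. But the article never says so, and its eligibility criteria and rationale do not support it. Condensing is not the explanation either: the comparator has not been left out but stated in two ways.

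Other parts of the defence stand.
- The article plans analyses for the total group and for each country separately, so differences between countries are not ignored. Those analyses still do not show what controls received.
- The cost-utility analysis draws on health care service use data, which should capture physiotherapy used by controls. Table 1 also leaves the economic study questions to be finalised in WP5. Costing is therefore partly covered; the RQ5 and WP5 wording is not.
- The Overview makes feasibility the primary outcome and efficacy preliminary, and the Discussion calls the trial exploratory. That limits the weight of any efficacy conclusion but does not settle what is being compared.
- The illustration rests entirely on assumed values. It shows the mechanism, not an error in a stated figure.

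**Conclusion.** The comparator is stated inconsistently in the current text, and this is wrong as written. Unless usual care is in-person physiotherapy for all controls, the randomised contrast does not estimate the efficacy, mood and quality-of-life, or cost-effectiveness comparisons in RQ3 to RQ5, and a nonsignificant difference could not be read as comparability with in-person therapy. The size cannot be fixed from the documents. Under the assumptions above (B of 0.3 or 0.5 SD, equal delivery modes), the contrast departs from RQ3's quantity by 0 to 0.5 SD, depending on what controls receive.

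Two stronger readings are not supported. A reader might infer that the trial cannot answer its questions at all. That is conditional on what usual care turns out to contain, and RQ3's question of whether a large trial is possible does not depend on it. A reader might also infer that the article makes opposite predictions for the two comparators. It does not: the only between-group mobility hypothesis is a nonsignificant difference, worded against usual care, and the Abstract's efficacy objective has no stated direction.

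**What to change.** Reconcile the Abstract, Overview, RQ3 to RQ5, the allocation text, Intervention and Comparators, and the cost-utility text to one comparator before the WP4 and WP5 ethics submissions. Which control is right is for the sponsor to decide.

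- **If the allocation text stands:** reword RQ3 to RQ5 and the WP5 objective as comparisons with usual care. Remove from RQ3 the in-person delivery phrase and the description of both arms as exercise programmes. Limit conclusions to the contrast with usual care.
- **If the in-person comparison is intended:** make the allocation, comparator and cost-utility text say so, along with the Abstract and the WP4 objective.

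In either case, report in-person physiotherapy received by arm and country, next to the per-country analyses already planned. The planned health care service use data are the natural source. The weekly FITT-VP reports are described as covering physical activity and are not stated to record who delivered a session, so they may need an added item on therapist-delivered sessions.

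The cost is protocol wording, one descriptive table and possibly one diary item. Ethical Considerations says the WP4 and WP5 applications are still to be submitted, so the change is cheap now. Once participants are randomised, the comparator cannot be changed.

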A particular strength of this study is its integration of technological innovation with a rigorous clinical and economic evaluation. By examining feasibility alongside psychometric testing and cost-effectiveness, the project will provide comprehensive insights into the practicality of scaling up such solutions in real-world settings. The inclusion of both patient-centered outcomes and system-level data will allow for a nuanced understanding of how AI-driven telerehabilitation can influence care delivery for people with MS. Still, as this is a protocol, all conclusions must remain provisional until data collection is complete. It will be important to interpret future findings with an understanding of the feasibility trial’s exploratory nature.

Several limitations and potential challenges should be acknowledged. First, as a feasibility study, the sample size may not be sufficient to detect small but clinically meaningful effects, and findings may not be generalizable beyond the populations and settings involved. Second, adherence to home-based interventions can be variable and difficult to monitor objectively outside controlled settings. To address this, we will incorporate remote use tracking, patient engagement strategies, and therapist follow-up. Third, technical issues such as hardware compatibility, internet connectivity, and user literacy may affect intervention delivery. These will be documented throughout the study and considered in the interpretation of results. Importantly, as with any AI-enabled solution, algorithm transparency, how well it can adapt to individual needs, and potential biases must be critically evaluated before broader deployment. Given that this is a feasibility protocol, any conclusions will remain provisional until the trial is completed and the data are evaluated.

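### RQ3 makes a nonsignificant between-group difference the result to be demonstrated, but failing to reject is not evidence of similar effects, and no margin or interval rule is stated

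*Protocol article*

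**What the plan says.** All references are to the protocol article.

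- **Research and Innovation Questions, RQ3.** The hypothesis has two parts. The first is "We hypothesize that both exercise intervention programs will improve mobility in people with MS". The second is that "nonsignificant differences in mobility outcome measures between groups (telerehabilitation vs usual care) will be demonstrated".
- **Same section, RQ4.** The question is whether the telerehabilitation program will "have a comparable effect on mood and quality of life (QoL) compared with standard physical therapy (facility based"). The hypothesis that follows is different: it predicts improvement in mood and quality of life among participants with marked symptoms at baseline.
- **Methodology, Approach, and Study Population.** On size: "We will include a target sample of 24 participants per country (in 4 countries; 96 participants in total"). The basis is a pilot-trial rule of thumb that "estimated the optimal sample size for an early-stage/pilot RCT to be 24". On levels of analysis: "Statistical analysis will be performed for the total group and each country separately". On allocation: "The participants will be randomly allocated (individual randomization) into one of two groups"; no ratio is given.
- **Outcome Measures for the Feasibility Multicenter RCT.** The 30-second sit-to-stand test (30STS) is labelled the primary outcome.
- **Data Analysis and Statistical Plan.** RQ3 and RQ4 outcomes go into linear mixed models for within-group and between-group effects. No equivalence or non-inferiority test, margin or interval criterion is mentioned.
- **Discussion.** The authors accept that "the sample size may not be sufficient to detect small but clinically meaningful effects". They do not connect this limit with the RQ3 hypothesis.

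**The concern.** A test of no difference can fail to reject because the arms are alike or because the trial is too imprecise to tell them apart. RQ3 does not separate the two: it names the nonsignificant result as the thing to be shown. The Discussion concedes that power for small but meaningful effects may be lacking, so the predicted between-group result is one that limited power makes likely even when such a difference exists.

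At stake is how WP4 will be read. If telerehabilitation is moderately worse than the comparator, the between-group half of RQ3 could still appear borne out, and that reading could carry into the design of the later trial. The risk is greatest in the single-country analyses of 24 people each. It is also an error in what the article states. A separate analysis plan could add a margin, but the published hypothesis would still need correcting.

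**Working it through.** **Inputs from the article.** 24 participants in each of 4 countries; two groups; individual randomization; pooled and per-country analyses.

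**Assumptions, because the article gives no figure.** Allocation 1:1; two-sided alpha 0.05 (one-sided 0.025 for non-inferiority); outcome in SD units; no dropout; a simple two-arm comparison standing in for the mixed model.

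**1. The plan's own figure.** 24 × 4 = 96, which matches. It rests on a rule of thumb, so there is no power calculation to reproduce. At 1:1 this gives 48 per arm pooled and 12 per arm in one country.

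**2. Chance of a nonsignificant result, unadjusted.** This is 1 − power of the two-sample t-test, from the noncentral t with 2n − 2 degrees of freedom and noncentrality d × √(n/2). For example, at n = 48 and d = 0.5 the noncentrality is 0.5 × √24 = 2.45, and power is 0.679.

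| True deficit (SD) | Pooled, 48 per arm | One country, 12 per arm |
|---|---|---|
| 0 | 95% | 95% |
| 0.2 | 84% | 92% |
| 0.3 | 69% | 89% |
| 0.4 | 51% | 85% |
| 0.5 | 32% | 78% |
| 0.8 | 3% | 53% |

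**3. With baseline adjustment.** The residual SD is multiplied by √(1 − r²): 0.866 at r = 0.5 and 0.714 at r = 0.7. A deficit of 0.3 SD becomes 0.346 or 0.420 residual SD, and one of 0.5 SD becomes 0.577 or 0.700. The pooled chance of nonsignificance is then 61% or 47% at 0.3 SD, and 20% or 8% at 0.5 SD.

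**4. Precision.** The unadjusted 95% CI half-width is t × √(2/n): 1.986 × 0.204 = 0.41 SD pooled, and 2.074 × 0.408 = 0.85 SD in one country.

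**5. What 96 participants could support as non-inferiority.** With a true difference of zero and 80% power, the margin is (1.96 + 0.842) × √(2/48) = 0.57 SD. With adjustment at r = 0.7 it is 0.57 × 0.714 = 0.41 SD. Unadjusted, margins of 0.3, 0.4 and 0.5 SD would need 175, 99 and 63 per arm.

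**6. The full two-part hypothesis.** Each arm's improvement was simulated with a two-sided 5% test, in change-score SD units, and required together with a nonsignificant between-arm test.

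| True gains (SD) | 48 per arm: both parts met | 12 per arm: both parts met |
|---|---|---|
| 0.5 and 0.5 | 83% | 12% |
| 0.2 and 0.7 | 18% | 5% |

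The joint hypothesis therefore becomes harder to meet as the sample shrinks. The between-group part alone behaves as in step 2.

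**The case against.** The best reply is that RQ3 is a prediction and not a decision rule. No section says that p above 0.05 will be taken as success or as grounds for adoption. The Overview makes trial feasibility the primary outcome, with efficacy preliminary; the Discussion calls the trial exploratory and its conclusions provisional, and looks ahead to a fully powered RCT. This lowers the consequence, but it does not repair the sentence: saying that nonsignificance will be demonstrated is still a wrong inference, and the article offers no other criterion for judging similarity.

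Three stronger readings are tempting and are not supported:

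- *The hypothesis would be confirmed whatever the truth.* The pooled test would miss a 0.8 SD deficit only about 3% of the time, and it would detect a 0.5 SD deficit 68% of the time.
- *The plan rewards noise.* The sentence also requires both arms to improve, and step 6 shows that a smaller sample makes the full hypothesis harder to meet. Only the between-group half is favored by imprecision. The improvement half does not rescue it, because two arms can both improve by different amounts.
- *RQ4 has the same fault.* RQ4 asks about comparability without a margin, but its hypothesis concerns improvement and does not predict nonsignificance.

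It is also fair that baseline adjustment lowers the pooled figures considerably. A formal margin test suits this trial poorly too: the sample is small, and the article itself calls usual care a broad term that varies between countries.

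**Conclusion.** The point holds for the between-group clause of RQ3. The clause treats failure to reject as the confirming result, with no margin or interval rule. Pooled, a true deficit of 0.3 SD would go undetected in about half to two-thirds of trials (47-69% across the adjusted and unadjusted calculations), and one of 0.5 SD in 8-32%. In a single country, unadjusted, the figures are 89% and 78%.

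These sizes rest on assumed 1:1 allocation, a two-sided 5% test, no dropout and, for the adjusted figures, a baseline correlation of 0.5 to 0.7. The logical error depends on none of them. The feasibility framing limits the harm, and the remedy is a correction of wording.

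**What to change.** In RQ3, replace the nonsignificance clause with wording such as: *The between-group difference in 30STS and the other mobility outcomes will be estimated with a 95% CI as exploratory; a p-value above 0.05 will not be read as comparability.* Repeat this in Data Analysis and Statistical Plan, for the pooled and the per-country analyses.

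Leave any comparability or non-inferiority claim, with a justified margin, to the fully powered RCT. Report the RQ4 question on comparable effects in the same form, as an estimate with its CI; its hypothesis needs no change on this account.

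The cost is a few sentences, with no change to sample size, data collection or models. The downside is that WP4 will make no comparability claim, which 96 participants could support only for a wide margin.
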